### Data management and analysis

Trial documentation including protocols, SOPs and CRFs will be shared electronically with participating study centres. Protocol amendments will be submitted to the Royal Brisbane and Women’s Hospital HREC and local site research governance offices and disseminated to the relevant parties at each study site. Data recorded on printed CRFs will be scanned to the study centre in Townsville where it will be entered centrally and examined for data quality. This will allow confirmation of entry criteria and collection of set entry and outcome data. Examples of important baseline data which will be collected include age, gender, presence of diabetes and/or dyslipidaemia, concurrent medications and maximum aortic diameter. At completion of the trial the database will be checked for errors and data confirmed with source documentation where required. Analysis of primary and secondary endpoints will be based on intention-to-treat at the time of randomisation. All participants who meet the eligibility criteria, provide written informed consent and are enrolled in the study will be included in the primary analysis, regardless of adherence to medication allocation.

To identify potential confounders, collected clinical and demographic data will be compared between groups via univariate statistics. The distribution of all continuous data variables will be assessed for normality using the Kolgorov-Smirnov test. Normally distributed continuous variables will be compared between test groups via *t* test; non-normally continuous distributed variables will be compared between groups using the Mann-Whitney *U* test. Nominal data will be compared using the chi-squared test. Characteristics showing a *p* value < 0.100 on univariate tests will be considered as potential confounders and will be entered as covariates in subsequent binary logistic regression models assessing the association of each of the outcome measures with treatment allocation. Following binary logistic regression, the association of all covariates with treatment allocation will be reported as odds ratios and 95% confidence intervals. For all analyses, *p* values <0.05 will be considered to be significant. Data will be published in a peer-reviewed journal with copies of the paper available to participants if required.

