## Methods/design

### Study design and participants

Fenofibrate in the management of AbdoMinal aortic anEurysm (FAME) is a multicentre, randomised, double-blind, placebo-controlled clinical trial to assess the effect of orally administered therapy with fenofibrate on key pathological markers of AAA in patients undergoing open AAA repair. The trial will be conducted at four sites in Australia: The Royal Brisbane and Women’s Hospital, Brisbane; The Holy Spirit Northside Private Hospital, Brisbane; The Townsville Hospital, Townsville and The Mater Hospital, Townsville. The trial will be reported according to the Standard Protocol Items: Recommendations for Intervention Trials (SPIRIT) (see Additional files 1 and 2). Only research personnel who are directly involved in the recruitment and data collection aspect of the study will have access to patients’ personal details. All Case Report Forms (CRFs), source documentation and samples will be stored de-identified where personal information has been removed and coded with a study number.

The FAME trial will include participants recruited from specialist vascular outpatient clinics who have an asymptomatic infrarenal AAA with a maximum orthogonal diameter ≥50 mm. FAME will not include individuals who require emergency or urgent AAA repair due to the requirement for a minimum 2 weeks of treatment with trial medication prior to surgery. Furthermore, participants will only be included if it is determined that they have a high likelihood of treatment compliance according to the treating physician or local study coordinator. Additional exclusion criteria include current treatment with fibrates, known contraindications to fenofibrate treatment and previous aortic surgery. A full list of inclusion and exclusion criteria is given in Table 1.

**Table 1 Tab1:** Patient eligibility criteria

Inclusion criteria
• Ability to provide written informed consent • Diagnosis with an asymptomatic AAA which is infrarenal in location and measures ≥50 mm on CTA • Scheduled for an elective open repair of an AAA • High likelihood of medication compliance within the 2-week period prior to surgery
Exclusion criteria

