### Randomisation and follow-up

The overall design of the FAME trial is shown in Fig. 1. At the initial visit, potential participants booked for an elective open repair of an AAA will be assessed against the eligibility criteria (Table 1) and, if appropriate, informed consent will be obtained. Individuals will undergo a medical examination, resting blood pressure and heart rate assessments, and collection of blood samples for measurement of full blood count (haemoglobin, white cell count, platelets, neutrophils, lymphocytes, monocytes, eosinophils, basophils), urea and electrolytes (sodium, potassium, creatinine, estimated glomerular filtration rate, urea, chloride, bicarbonate), liver function tests (Albumin, total bilirubin, alanine transaminase, aspartate aminotransferase, gamma-glutamyl transpeptidase, lactate dehydrogenase), fasting lipids (cholesterol, triglyceride, HDL cholesterol, low-density lipoprotein (LDL) cholesterol), fasting glucose and C-reactive protein. Serum, plasma and whole blood will also be collected for the later assessment of circulating concentrations of protein (such as cytokines) and genetic (deoxyribonucleic acid (DNA) and ribonucleic acid (RNA)) markers. Investigational blood samples will be collected into the following tubes: 2 × 5-mL SST, 2 × 4-mL EDTA tubes, 1 × 4-mL sodium citrate tube and 1 × 2.5-mL PaxGene tube. Blood samples will be processed according to site-specific standard operating procedures (SOPs) and shipped to the study centre in Townsville. Eligible participants will be randomised to receive 145 mg fenofibrate or placebo, administered once a day for a minimum of 2 weeks directly prior to surgery, in a parallel-group design. Randomisation to fenofibrate or placebo will be stratified by study centre. Random allocation sequences will be computer-generated by a statistician and provided to each study centre's clinical trial pharmacist, ensuring both investigators and participants are blinded to drug assignment. Trial medication will be allocated and dispensed by the local study centre’s clinical trials pharmacist. Allocation concealment will be achieved by using identical packaging of the intervention and placebo. In the case of an emergency situation where breaking of the group allocation blinding would be required, the local study centre clinical trial pharmacist will be contacted. To facilitate compliance, participants will be provided with the phone number of the local study coordinator with instructions to contact them in the event of possible medication-related problems or consideration of discontinuation. In this event arrangements will be made for the participant to be reviewed by the study physician to ascertain whether discontinuation is required.

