### Outcome assessment

Outcome assessment will be performed at the study centre in Townsville on the tissue and blood samples collected. All outcome assessment will be conducted by scientists blinded to the treatment allocation of the participants.

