### Study population and power calculation

Estimated outcomes for the control group are based on assessments performed in human AAA biopsies or blood samples from previous studies [28, 32, 42–44]. Estimated effect sizes for fenofibrate therapy are based on previous rodent and human studies, and the consideration of outcomes likely to be required for clinical efficacy [19, 28, 32, 42–44]. To significantly influence the natural history of aortic destruction, it is estimated that a reduction in all primary outcomes assessed within AAA biopsies of at least 50% is likely to be required. In a rodent model, 4 weeks’ treatment with fenofibrate reduced aortic OPN concentration and macrophage infiltration by a median of 95% and 70%, respectively, suggesting that this treatment effect size is realistic [19]. For serum OPN, it has previously been reported that a fibrate reduced circulating OPN concentration by approximately 40% after 4 weeks of treatment [32]. Based on these data, the estimated mean values for control and treatment groups were calculated and are given in Table 2. Sample sizes were calculated using GPower3.1, based on a *t* test as the statistical analysis test. Since there are three primary outcomes, alpha was set at .017, adjusted from .05 for multiple testing. Sample size was estimated based on a power of 80% and equal numbers of participants in each treatment arm. As a result, 20 participants receiving fenofibrate and 20 participants receiving placebo are required. Assuming a dropout rate of 5%, a total of 42 participants will be required.

**Table 2 Tab2:** Summary of primary outcome measures and expected results

Primary outcome	Measurement method	Estimated outcomes	
		Placebo	Fenofibrate
AAA-wall OPN concentration (pg/mg)	ELISA	210 ± 145	84 ± 87
AAA-wall macrophages (per mm^2^ section)	IHC	4.9 ± 1.8	2.4 ± 1.8
Serum OPN concentration (ng/mL)	ELISA	77 ± 32	46 ± 32

*AAA* abdominal aortic aneurysm, *ELISA* enzyme-linked immunosorbent assay, *IHC* immunohistochemistry, *OPN* osteopontin

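### Choosing covariates by a baseline p < 0.10 test between arms selects on chance imbalance, costs precision, and is very unlikely to admit study centre, the stratification factor

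*Protocol article*

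**What the plan says.** In the protocol article, section Data management and analysis, "collected clinical and demographic data will be compared between groups via univariate statistics". Those with a p "value < 0.100 on univariate tests will be considered as potential confounders and will be entered as covariates". The models they enter are also named there: selected characteristics are "entered as covariates in subsequent binary logistic regression models assessing the association of each of the outcome measures with treatment allocation". No covariate is named in advance, and the number of characteristics to be screened is not given.

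The section Randomisation and follow-up says: "Randomisation to fenofibrate or placebo will be stratified by study centre". There are four centres (Study design and participants). The analysis section does not mention centre, so on the text shown its only route into the model is the p < 0.10 screen.

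The section Study population and power calculation sizes the trial on a t test without covariates, at alpha 0.017 for each of three primary outcomes.

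**The concern.** A covariate helps in a randomised trial when it predicts the outcome. A test between randomised arms says nothing about that: it asks whether the arms differ, and under valid randomisation they differ only by chance. Three things follow from the stated rule.

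- A selected variable is, by construction, correlated with treatment in this sample. If it does not predict the outcome, it widens the standard error of the treatment effect and gives nothing back.
- The model, and so the adjusted estimate, depends on which imbalances happen to occur. It cannot be written down until the arms are compared.
- The rule works against the one factor that the design singles out. Stratification balances centre across arms, so centre should almost never reach p < 0.10, even if sites differ in outcome.

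At stake is precision in a trial of 40 evaluable participants whose sample size leaves no reserve for such a loss.

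**Working it through.** **1. The plan's own figure.** From Table 2, serum OPN has d = (77 − 46)/32 = 0.969, the smallest of the three effects. Noncentral-t power with 20 per arm is 0.803 at one-sided 0.017 and 0.713 at two-sided 0.017. The stated 20 per arm therefore reproduces with a one-sided test; a two-sided test needs 24 per arm. The article does not state sidedness. Below I use two-sided 0.017, so the reference power is 71%.

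**2. How many variables could be screened.** The article does not say, so I take a range.
- Narrow: the six examples in the analysis section (age, gender, diabetes, dyslipidaemia, concurrent medications, aortic diameter).
- Broad: these six, plus the initial-visit laboratory values (8 blood count + 7 electrolyte and renal + 6 liver + 4 lipid + glucose + C-reactive protein = 27), plus systolic pressure, diastolic pressure and heart rate (3). Total 6 + 27 + 3 = 36.

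**3. Chance entries.** With k candidates, the expected number entering is 0.10k. The chance of at least one is 1 − 0.9^k if they are independent.

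| k | Expected entries | Chance of at least one |
|---|---|---|
| 6 | 0.6 | 47% |
| 20 | 2.0 | 88% |
| 36 | 3.6 | 98% (93% with pairwise correlation 0.3) |

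**4. Why each entry costs precision.** With 40 participants, p < 0.10 means |t| > 1.686 on 38 df. The squared correlation with treatment is then at least 1.686²/(1.686² + 38) = 2.84/40.84 = 0.070. The variance of the treatment effect is multiplied by at least 1/(1 − 0.070) = 1.075, so its standard error rises by at least 3.7% for a single pure-noise covariate.

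**5. Effect on power.** Simulation: linear model with the outcome as dependent variable, 20 per arm, d = 0.969, two-sided 0.017, pure-noise candidates. The ranges cover separate runs and, in part, correlated candidates. With 3,000 runs the Monte Carlo standard error is about √(0.71 × 0.29/3000) = 0.8 points.

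| Candidates | Power, serum OPN |
|---|---|
| none (unadjusted) | about 71% |
| 6 | 67–69% |
| 20 | 59–63% |
| about 36 | 51–58% |

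Under the null, rejection stayed near 0.017 (0.015–0.019).

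**6. Against pre-specification.** With 15 candidates, one of them prognostic, and no centre effect:

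| Correlation of the prognostic covariate with the outcome | p < 0.10 rule | Unadjusted | That covariate pre-specified |
|---|---|---|---|
| 0.3 | 0.629 | 0.708 | 0.741 |
| 0.5 | 0.639 | 0.708 | 0.826 |

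The rule gives up 11 and 19 points against naming the covariate in advance.

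**7. Centre.** Four centres of 10, centre term against no centre term, prognostic correlation 0.3:

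| Centre share of variance | Without centre | With centre |
|---|---|---|
| 0% | 0.708 | 0.705 |
| 5% | 0.724 | 0.743 |
| 10% | 0.715 | 0.754 |
| 20% | 0.735 | 0.819 |

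Omitting centre costs about 0, 2, 4 and 8 points. At 20% the unadjusted test is also conservative, with rejection under the null of about 0.008 against 0.017.

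**The case against.** The strongest reply concerns size and scope.

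- **Number of candidates.** No text says that every safety laboratory value will be screened. On the section's own six examples the loss is only about 2 to 4 points. This stands: 36 is the broadest reading, and the result must be given as a range.
- **Prognostic candidates.** Some could predict the outcome. With five prognostic variables (r = 0.3) among six candidates, simulated power was unchanged at 71%. It would be wrong to say that the selected variables explain nothing. The rule still does not select them for that reason.
- **Other outcomes.** Serum OPN is the weakest case. For macrophages (d = 1.389) power is about 97% unadjusted, and still about 92% with 20 candidates and 86% with 35.
- **Model.** The article specifies logistic regression with treatment allocation as the dependent variable, not the linear model used here. Simulated literally (15 candidates, one prognostic at r = 0.5), power was 0.52 by Wald test and 0.69 by likelihood ratio, against 0.70 for the t test. The size of the loss therefore also depends on the test. The direction of that regression is a separate issue.
- **Centre.** An article may leave the handling of the stratification factor to the full protocol or the SAP, and silence alone would be no finding. Central, blinded outcome assessment in Townsville, with all macrophage sections stained together, also limits site variation, although collection follows site-specific procedures. What stands is narrower: the one entry rule that is stated is very unlikely to let centre in.

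A reader might also infer that covariates are picked on unblinded data. The documents do not support this. The comparison needs data split by randomised group, but coded labels are possible and nothing excludes them.

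**Conclusion.** The point holds as a defect in a stated rule, not as a gap in a condensed article: a later SAP could repair it only by departing from the text. Followed as written, the rule selects covariates on chance imbalance, leaves the model open until the arms are compared, and tends to exclude the stratification factor.

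For serum OPN the loss runs from about 2 points (6 noise candidates) to about 20 points (some 36), from a reference of 71%. This assumes pure-noise candidates, a linear model and two-sided 0.017. It shrinks or vanishes when candidates are prognostic, and it is smaller for macrophages. The further cost of omitting centre, 0 to 8 points, rests on a centre effect that the documents do not give.

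A reader might infer that data-driven selection inflates false positives. The linear-model checks do not show this: rejection under the null stayed near nominal with noise candidates and fell below it when an ignored centre effect was large. The harm is to precision and to the stability of the estimate. The change should be made, but the trial does not fail without it.

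**What to change.** Delete the p < 0.10 rule and the baseline significance tests, and describe baseline characteristics by arm without p values. For the primary models, with the outcome as dependent variable, pre-specify:

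- study centre, pooled by city (Brisbane, Townsville) if sites are small;
- baseline serum OPN for the serum outcome, which is obtainable because serum is taken at the initial visit and again on the day of surgery;
- at most one or two further prognostic covariates, named before the groups are compared. Maximum aortic diameter is one possibility; other choices are defensible if fixed in advance.

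The cost is an amendment of wording, which was feasible at submission because recruitment was still under way. Centre uses 3 degrees of freedom (1 if pooled by city). If centre has no effect, this costs under one point of power (0.708 to 0.705 in the check above). The baseline serum must also be assayed for OPN if that is not already planned.

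### The adjusted analysis makes treatment allocation the dependent variable, so it yields odds ratios for allocation rather than an effect of fenofibrate on the biomarkers

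*Protocol article*

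**What the plan says.** Under Data management and analysis, the protocol article compares clinical and demographic data between arms, with this screening rule: "Characteristics showing a *p* value < 0.100 on univariate tests will be considered as potential confounders". The selected characteristics then enter "binary logistic regression models assessing the association of each of the outcome measures with treatment allocation". On reporting it says that "the association of all covariates with treatment allocation will be reported as odds ratios and 95% confidence intervals".

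Under Study population and power calculation, the sample size is "based on a *t* test as the statistical analysis test". Table 2 gives all three primary outcomes as means and SDs on continuous scales: wall osteopontin (OPN) in pg/mg, wall macrophages per mm², and serum OPN in ng/mL. The same section says that a reduction of at least 50% is probably needed for the tissue outcomes, and cites a reduction of about 40% in circulating OPN with a fibrate.

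**The concern.** The trial asks by how much fenofibrate lowers three biomarkers. That calls for a model with the biomarker on the left and the arm on the right. The adjusted model stated here runs the other way: it estimates how the odds of having been randomised to fenofibrate change per unit of a biomarker measured after treatment began.

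Allocation was fixed by the randomisation list, so these odds describe nothing that the drug does. A reader of the results could not tell from such an odds ratio whether wall macrophages fell by half. The odds ratios for the other covariates would only describe baseline imbalance, which under randomisation is due to chance.

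**Working it through.** **1. Which variable is the dependent one.** A binary logistic model needs a binary dependent variable. Table 2 gives three continuous outcomes and the article states no threshold for any of them, which leaves the arm. The reporting sentence agrees, since it gives odds ratios for association with allocation.

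**2. The plan's own sample size.** From Table 2:
- Serum OPN: d = (77 − 46)/32 = 0.969, the smallest effect, so it drives the sample size.
- Wall OPN: pooled SD = √((145² + 87²)/2) = 119.6; d = 126/119.6 = 1.054.
- Macrophages: d = 2.5/1.8 = 1.389.

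Exact noncentral-t power for serum OPN with 20 per arm at .017 is 80.3% one-sided and 71% two-sided. The stated 20 per arm therefore reproduces with a one-sided t test; a two-sided test would need 24. The article does not state sidedness. Either way, the quantity behind the sample size is a difference in means.

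**3. What the odds ratio measures.** For normal data with a common SD, the slope of the reversed model is

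log OR per unit = (mean on fenofibrate − mean on placebo)/SD².

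- Serum OPN as planned: −31/32² = −31/1024 = −0.0303, so OR = 0.970 per ng/mL.
- The same 31 ng/mL reduction with an assumed SD of 16: −31/256 = −0.1211, so OR = 0.886 per ng/mL.

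The drug effect is identical, but the log odds ratio is four times as large. The odds ratio depends on the spread of the biomarker and cannot be turned into a reduction without more information.

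For wall OPN the planned SDs differ (145 and 87). The log odds of allocation then contain a squared term with coefficient ½(1/145² − 1/87²) = −0.0000423. A model linear in the biomarker is thus misspecified under the plan's own figures.

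**4. What the reversal costs in power.** Simulated normal data with the Table 2 means and SDs, 20 per arm, two-sided, no covariates:

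| Outcome | Level | t test | Logistic, Wald | Logistic, likelihood ratio |
|---|---|---|---|---|
| Serum OPN | .017 | 71% | 62% | 74% |
| Serum OPN | .05 | 85% | 82% | 86–87% |
| Wall OPN | .017 | 79% | 70% | 82% |
| Macrophages | .017 | 97% | 94% | 97% |

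Both levels are shown because the article gives both. The sample-size section says "Since there are three primary outcomes, alpha was set at .017, adjusted from .05 for multiple testing"; the analysis section says "For all analyses, *p* values <0.05 will be considered to be significant".

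**5. What the covariate screen costs.** Serum OPN, two-sided .017, with covariates entered when p < 0.10 between arms. The number of characteristics screened is an assumption, and all of them are unrelated to outcome:

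| Candidates | Linear model | Logistic, Wald | Logistic, likelihood ratio |
|---|---|---|---|
| 5 | 69% | 59% | 72% |
| 10 | 66% | 55% | 70% |
| 20 | 60% | 47% | 65% |

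With 35 candidates, Wald falls to about 34% and the linear model to about 54%. Measured from the t test's 71%, the Wald loss with 20 candidates is 71 − 47 = 24 points, and the linear model alone loses 71 − 60 = 11. Nearly half of the drop therefore comes from choosing covariates by between-arm p-value, not from the direction of the model.

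**The case against.** The reversed model is still a valid way to ask whether arm and biomarker are associated, and with a likelihood-ratio test it gives up no power. The t-test and Mann-Whitney sentences in the same section are worded for continuous variables in general. They stand in the paragraph on finding confounders, but could also cover the outcomes; an unadjusted comparison of the kind the trial was sized for would then exist alongside.

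Both points stand, and they rule out two stronger readings.

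- A reader might infer that the trial cannot answer its own question. The text does not support this, because association can be tested and an unadjusted comparison may be intended.
- A reader might infer that the reversal loses much of the planned power. It does not in general. At one-sided .017, the variant that reproduces 20 per arm, serum OPN power is 80% for the t test, 76% for Wald and 82% for the likelihood ratio. At two-sided .05 even Wald reaches 82%, above the planned 80%. Without covariates, separation is practically absent at the planned effects.

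Some of the likelihood-ratio advantage is not real: with covariates its type I error is 6.4–7.0% at a nominal 5%.

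One might also suppose that the outcomes are to be dichotomised, which would make them the dependent variables. No cut-point is stated, and the reporting sentence names allocation.

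None of this rescues the estimate. The article commits to the type of model, its direction and its reported quantity, so this is not a detail left to an analysis plan.

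**Conclusion.** The point holds as a wrong estimand in the adjusted analysis and a mismatch with the basis of the sample size. As worded, the adjusted result for every primary outcome is an odds ratio for allocation, which expresses neither a mean difference nor a percentage reduction. This follows from the text and from the scales in Table 2, without simulation.

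The effect on power is secondary and conditional. For serum OPN without covariates at two-sided .017, it is about 9 points with a Wald test and none with a likelihood-ratio test; at .05 the Wald cost is about 3 points. The much larger Wald losses need an assumed 20 or 35 screened characteristics and are partly due to the screening rule. The power figures assume normal outcomes, independent covariates unrelated to outcome, and a choice of test and sidedness that the article does not state.

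**What to change.** Replace the logistic models. For each primary outcome, fit a linear model with the biomarker as dependent variable (log-transformed if skewed) and treatment arm as explanatory variable. Adjust for study centre, which is the stratification factor, and for serum OPN also for the baseline value from the initial-visit sample. Report the adjusted mean difference, or the fenofibrate-to-placebo ratio on the log scale, with its confidence interval. Delete the sentence on odds ratios for allocation. Naming the covariates in advance also removes the need for the p < 0.100 screen.

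Without covariates the linear model has the power of the t test (71% for serum OPN at two-sided .017). With a baseline covariate of assumed correlation 0.3, 0.5 or 0.7 with the outcome, it reaches 75%, 84% or 96%; the reversed Wald test on the same data gives 66%, 77% or 92%, and the likelihood-ratio test 79%, 87% or 96%. The main gain is an estimate in interpretable units.

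The cost is a change of wording in the analysis section. No new participants or samples are needed, since serum is already drawn at the initial visit; the stored sample must be assayed for OPN if that is not already planned. Recruitment was still ongoing when the article was submitted. If the analysis has not yet been run, the change can be made before unblinding.

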**Methods/design:**

Fenofibrate in the management of AbdoMinal aortic anEurysm (FAME) is a multicentre, randomised, double-blind, placebo-controlled clinical trial to assess the effect of orally administered therapy with fenofibrate on key pathological markers of AAA in patients undergoing open AAA repair. A total of 42 participants scheduled for an elective open AAA repair will be randomly assigned to either 145 mg of fenofibrate per day or identical placebo for a minimum period of 2 weeks prior to surgery. Primary outcome measures will be macrophage number and osteopontin (OPN) concentration within the AAA wall as well as serum concentrations of OPN. Secondary outcome measures will include levels of matrix metalloproteinases and proinflammatory cytokines within the AAA wall, periaortic fat and intramural thrombus and circulating concentrations of AAA biomarkers.

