### Secondary outcome assessment

Additionally, inflammatory cells (neutrophils, B- and T-lymphocytes), MMPs and proinflammatory cytokines will be assessed by immunohistochemistry and ELISA as previously described [40, 41]. Circulating concentrations of other AAA biomarkers, including osteoprotegerin, resistin, D-dimer and fasting lipids, will be assessed by ELISA and automated assays as previously described [31, 36–38]. Whole genome microarrays and real-time polymerase chain reaction will be used to examine gene expression levels based on findings from ongoing expression arrays and biomarker studies.

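### The three primary outcomes are sized at alpha .017 for multiplicity, but the analysis section sets significance at 0.05 for every analysis; family-wise error could reach about 14%

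*Protocol article*

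**What the plan says.** The abstract of the protocol article names three primary outcomes: "Primary outcome measures will be macrophage number and osteopontin (OPN) concentration within the AAA wall as well as serum concentrations of OPN".

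The section Study population and power calculation adjusts for there being three: "Since there are three primary outcomes, alpha was set at .017, adjusted from .05 for multiple testing". It adds "Sample sizes were calculated using GPower3.1" with a t test, and "Sample size was estimated based on a power of 80% and equal numbers of participants in each treatment arm". The result is 20 per arm, then "Assuming a dropout rate of 5%, a total of 42 participants will be required". It does not say whether the test is one-sided or two-sided.

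The section Data management and analysis covers the primaries explicitly: "Analysis of primary and secondary endpoints will be based on intention-to-treat at the time of randomisation". After describing the group comparisons and the regression models for each outcome, it closes with a single threshold, applied to all analyses: p "values <0.05 will be considered to be significant". The article gives no exception for the primary outcomes, no adjusted p values, no testing order and no rule that all three must succeed.

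**The concern.** An alpha split protects against false positives only if it is used when results are declared significant. Sizing at .017 and then deciding at 0.05 raises power and controls nothing.

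The conflict has practical consequences. A primary p value between .017 and .05 is significant under the analysis section and not significant under the sample size section. In a trial of 42 participants such a value is quite possible. With both rules in print, the choice between them could be made after the results are known.

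This is not a detail left to an unseen analysis plan. The article itself states two thresholds for the same tests, and any analysis plan would have to depart from one of them.

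**Working it through.** **Inputs.** Table 2 of the protocol article gives placebo and fenofibrate means ± SD:
- serum OPN: 77 ± 32 and 46 ± 32 ng/mL
- wall OPN: 210 ± 145 and 84 ± 87 pg/mg
- wall macrophages: 4.9 ± 1.8 and 2.4 ± 1.8 per mm²

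Alpha .017, power 80%, equal arms and 5% dropout come from the power section. Sidedness is not stated, so both were tried.

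**Standardised effects.**
- Serum OPN: (77 − 46)/32 = 0.969.
- Wall OPN: pooled SD = √[(145² + 87²)/2] = 119.6, so 126/119.6 = 1.054.
- Macrophages: 2.5/1.8 = 1.389.

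**Reproducing the plan's sample size** (two-sample t test, exact noncentral t power, alpha .017):

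| Outcome | n per arm, one-sided | Power at 20, one-sided | n per arm, two-sided | Power at 20, two-sided |
|---|---|---|---|---|
| Serum OPN | 20 | 80.3% | 24 | 71.3% |
| Wall OPN | 17 | 86.7% | 21 | 79.4% |
| Macrophages | 11 | 98.4% | 13 | 96.7% |

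The stated 20 per arm is reproduced by serum OPN, the outcome needing the most participants, with a one-sided test. The total follows as 40 × 1.05 = 42. (Dividing instead, 40/0.95 = 42.1, rounds up to 43; the difference is immaterial here.) So .017 was genuinely used for sizing.

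**Family-wise error, independent outcomes:** 1 − (1 − α)³.
- At 0.05 each: 1 − 0.95³ = 0.1426, or 14.3%. The bound under any dependence is 3 × 0.05 = 15%.
- At .017 each: 1 − 0.983³ = 0.0501, or 5.0% (bound 5.1%).
- At exactly .05/3 each: 4.9% (bound 5.0%).

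**Family-wise error, correlated outcomes.** The documents give no correlations, so a common value was assumed. Three two-sided z tests were simulated with 2 million draws:

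| Assumed correlation | 0.05 each | .017 each |
|---|---|---|
| 0 | 14.3% | 5.0% |
| 0.3 | 13.6% | 4.9% |
| 0.5 | 12.5% | 4.5% |
| 0.8 | 9.8% | 3.6% |
| 0.9 | 8.4% | 3.1% |

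At every assumed value the 0.05 rule exceeds 5%, while the .017 rule stays at about 5% or below.

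**Power under Holm.** Simulating the Table 2 effects with 20 per arm, two-sided t tests and correlations of 0 to 0.8, Holm rejects for serum OPN in about 82% to 83% of trials, because the other two outcomes usually pass first. If serum OPN is the only real effect, Holm usually tests it near .0167, and two-sided power is then about 71%.

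**The case against.** **The outcomes are likely to be correlated.** The Background says that OPN promotes macrophage accumulation and that fenofibrate reduced both in a rodent study. This stands. A reader might infer that the error rate simply becomes 14%; that is the independence figure, close to the upper bound, and the fair statement is up to about 14%.

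**No trial-level success rule is stated.** A reader might infer that any one primary at p<0.05 makes the trial positive, but the article does not say so. The aims are listed jointly, and the power section says that a reduction of at least half in all the biopsy outcomes is probably needed. If all three had to succeed, 0.05 each would be valid. But the remark on biopsy outcomes justifies the effect size, does not cover serum OPN and is not a decision rule, and an alpha split would be unnecessary under an all-must-succeed rule. The error figure therefore rests on the condition that the outcomes are claimed separately, which the split implies.

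**The 0.05 sentence might concern only the regressions or the confounder screen.** This does not stand. The screen has its own cut-off of 0.100, the regressions cover each outcome measure, and the sentence is not limited.

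**Gene expression.** The article also says "Whole genome microarrays and real-time polymerase chain reaction will be used to examine gene expression levels". A reader might infer that p<0.05 would be applied gene by gene and give mostly false positives. The documents do not support this. The share of false positives depends on how many genes truly change and on power, neither of which is given, and array analysis is a detail that a condensed article commonly leaves elsewhere. It forms no part of this point.

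**Conclusion.** The contradiction is real and explicit: .017 per primary outcome in the power section, 0.05 for everything in the analysis section. It concerns a decision threshold and should be resolved before unblinding.

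If the three outcomes are claimed separately at 0.05, the chance of at least one false-positive primary is up to about 14% against the intended 5%. The range of about 8% to 14% rests on assumed common correlations of 0.9 down to 0, and on no true effect on any of the three.

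Sidedness belongs to the same repair, since the printed sample size fits a one-sided test at .017 and not a two-sided one. A reader might infer that moving to a two-sided Holm procedure could never lose power against the sizing. That holds only at equal sidedness.

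**What to change.** In Data management and analysis, replace the closing threshold sentence with wording to this effect: *The three primary outcomes are tested at a family-wise alpha of 0.05, at .017 each [or by the Holm procedure: smallest p against .0167, next against .025, largest against .05]. Tests are [one-sided/two-sided]. Secondary outcomes are reported at nominal 0.05 and are exploratory.*

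Keeping .017 each is the smallest change and matches the power section; .0167 would remove the rounding excess. Holm is optional. At the same sidedness it is at least as powerful as .05/3 each.

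State the sidedness in the power section too, and restate power to match:
- One-sided at .017: 20 per arm stands (80.3% for serum OPN).
- Two-sided at .017: report 71.3% for serum OPN at 20 per arm, or plan for 24 per arm.
- Two-sided Holm: about 82% to 83% for serum OPN if all three planned effects hold, but about 71% if serum OPN is the only real effect.

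The cost is a short change of wording and a restated power figure, with no change to sample size if the one-sided .017 rule is kept. The downside is that a primary p value between .017 and .05 may no longer count as significant. The article reports recruitment still under way at submission, so at that point the rule could still be settled before unblinding.
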